## 4. Conclusions

The MED4Youth project aims at determining whether an MD-based intervention including sourdough bread and healthy Mediterranean foods (chickpeas, humus, mixed nuts, and pomegranate juice) is more effective than a standard low-fat diet to tackle youth obesity, by conducting a multicenter randomized controlled trial with 240 overweight and obese adolescents from Spain, Portugal, and Italy. The dietary interventions will also include ICT educational tools. The scientific data derived from this project, especially those generated by the application of omics technologies, are expected to provide a deeper understanding of the mechanisms implicated in the beneficial effects of MD against youth obesity and the associated CVD risks factors, as well as the role of the gut microbiota. The MED4Youth project will help to establish an effective intervention for obese adolescents and therefore will help to prevent adult obesity and its comorbidities. Public health policies for obesity prevention could also be supported by the results of this project.

Further studies on larger cohorts would be crucial for the validation of the health biomarkers analyzed in the MED4Youth project in order to clearly demonstrate the underlying mechanisms behind the effects of MD against youth obesity and the associated risk factors. Moreover, on the basis of the results obtained through the analysis of food intake biomarkers in the present study, future studies could be designed to unravel which specific foods or bioactive compounds present in the MD are involved in the beneficial effects described for this dietary pattern.

## Figures and Tables

**Figure 1 ijerph-18-04841-f001:**
[figure not shown]
(**a**) Design of the Study. (**b**) Overview of the intervention groups. MD, Mediterranean Diet; MED, Mediterranean; BMI, Body Mass Index; ES, Spain; PT, Portugal; IT, Italy; V, Visit; WC, Waist Circumference.

**Table 1 ijerph-18-04841-t001:** Details on the frequency portions of the Mediterranean basin foods.

Specific Food	Frequency of Portions
Pomegranate	It is recommended at least 2 servings/day of fruit: 14–21 servings/week In addition to the fresh whole fruit, 4 servings of pomegranate juice (200 mL) will be consumed during the week.
Hummus and chickpeas	It is recommended 3 servings/week of pulses (150–200 g (50–80 g dry)). Two servings/week must be cooked chickpeas, minimum one of them as hummus, and another serving may be chickpeas or different pulses. The portion size of hummus is 200 g.
Nuts (almonds, walnuts, and hazelnuts)	It is recommended 3 servings/week: 30 g of mixed nuts/serving. Four servings will be consumed to properly combine the 4 food items included in the MD along the week. Mixed nuts will be walnuts, almonds, and hazelnuts.
Sourdough bread	It is recommended 4–6 servings/day of cereals. Two of these must be a serving of sourdough bread (1 serving of bread is approximately 50–60 g [46,47]).

**Table 2 ijerph-18-04841-t002:** Variables to be analyzed.

Variables	Tool	Timeline
Blood pressure, weight, height, BMI, body composition, WC, WHR	Dietitians/Nutritionists	V1, V2, V3, V4
Physical activity	PAQ-A *	V1, V2, V3, V4
Dietary intake	3-day dietary record *	V1, V2, V3, V4
Food habits	FFQ Helena questionnaire *	V1, V2, V3, V4
MD adherence	KidMed questionnaire *	V1, V2, V3, V4
Quality of life	Kidscreen-27 questionnaire *	V1, V2, V3, V4
Sociodemographic data	HBSC questionnaire *	V1
Knowledge on food and nutrition	NK Helena questionnaire *	V1, V3, V4
Microbiota (feces)	16sRNA sequencing	V1 and V3
Gut-derived metabolites (LPS, SCFAs, lactate, bile acids) (feces and/or plasma)	NMR/GC-MS	V1 and V3
Biomarkers of oxidative stress (8-OHdG, F2-isoprostanes) (urine)	ELISA	V1 and V3
Biomarkers of inflammation (IL-6, CRP, TNFα, MCP1, IL-8) (plasma)	Magnetic bead-based multiplex assays Homeostatic Model Assessment for insulin resistance	V1 and V3 V1 and V3
Biomarkers of adipose tissue function (adiponectin, leptin, resistin) (plasma)		
Biomarkers of insulin resistance (plasma)		
Biomarkers of cardiovascular risk (TMAO) (plasma and urine)	UHPLC‑MS	
Circulating levels of glucose and blood lipid profile	Enzymatic assays	V1 and V3
Key food intake biomarkers and phenolic metabolites (urine)	Targeted metabolomics (UHPLC‑MS)	V1 and V3
Advanced glycation end products (AGEs) related analyses (plasma or erythrocytes)	ELISA / enzymatic assays	V1 and V3

V: visit; BMI: body mass index; WC: waist circumference; WHR: waist–hip ratio; MD: Mediterranean diet; LPS: lipopolysaccharides; SCFAs: short-chain fatty acids; IL-6: interleukin 6; CRP: C-reactive protein; TNFa: tumor necrosis factor alpha; MCP1: monocyte chemoattractant protein-1; IL-8: interleukin 8; TMAO: trimethylamine N-oxide; PAQ: physical activity questionnaire; FFQ: food frequency questionnaire; HBSC: health behavior in school-aged children; NKQ: nutrition knowledge questionnaire; NMR: nuclear magnetic resonance; GC-MS: gas chromatography coupled to mass spectrometry; ELISA: enzyme-linked immunosorbent assay; UHPLC-GC ultrahigh-pressure liquid chromatography coupled to mass spectrometry. * These variables will be collected through the app.

**Table 3 ijerph-18-04841-t003:** Description of study visits.

Visit	Type of Visit	Description
0	pre-screening visit before randomization	To check inclusion/exclusion criteria in the study
1	after randomization, inclusion visit	Feces, urine, and blood samples will be collected, anthropometric and blood pressure will be measured, and questionnaires (food, knowledge and physical activity) and dietary records will be completed.
2	after 2 months	Anthropometric and blood pressure will be measured, and questionnaires (food, knowledge and physical activity) and dietary records will be completed.
3	after 4 months, final study visit	Feces, urine, and blood samples will be collected, anthropometric and blood pressure will be measured, and questionnaires (food, knowledge and physical activity) and dietary records will be completed.
4	visit 4 months after the end of the intervention	Anthropometric and blood pressure will be measured, and questionnaires (food, knowledge and physical activity) and dietary records will be completed.

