For ethical reasons, a control group with no treatment against obesity will not be included, since a meta-analysis of randomized controlled trials for the treatment of overweight in children clearly demonstrates that control groups, whether wait listed or only given written information, consistently gained weight (2.1% increase in percentage overweight post treatment and 2.7% post follow-up) [40]. Due to the nature of the study, the participants cannot be blinded to the intervention, although the investigators who will perform the sample and data analysis will be.

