### 2.2. Selection Criteria

Subjects included in the study:Boys and girls aged 13–17 years,Having obesity, defined as an age- and sex-specific BMI in the 95th percentile or greater (1), or great overweight (age- and sex-specific BMI in the ≥90th to <95th percentile),If they and their parents (or holders of parental responsibility over the child) provide written informed consent (signed by parents and by the adolescent), andHaving easily access to internet (e.g., via mobile phone, tablet, pc).

Exclusion criteria are:Having diabetes and other metabolic, endocrine, and chronic disorders,Intake of antibiotics, drug, probiotics, or nutritional supplements in the last month,Prescribed medicine to control hypertension, inflammation, or dyslipidaemia,Following a prescribed diet for any reason, including weight loss, in the last 3 months,Following a religion-restricted diet, andHaving allergies or food intolerances to nuts, pomegranate, bread, and/or chickpeas.

All volunteers will be examined by physician to assess whether they meet the conditions for inclusion. For this purpose, a medical interview, a physical examination, and laboratory tests will be performed.

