### 2.3. Dietary Interventions

Both diets (MD and low-fat diet) will be implemented by dietitians/nutritionists from each center. First of all, the total energy requirements of adolescents will be calculated by using the Molnar equation [41], and the level of physical activity will be obtained from the validated Physical Activity Questionnaire for Adolescents (PAQ-A). Afterwards, a caloric restriction of 20% will be applied to design a personalized diet for each obese individual (BMI ≥95th percentile) [42], while caloric restriction will be carefully evaluated for each individual with great overweight (BMI ≥90 to <95th percentile). For ethical issues, adolescents will not be conscious about caloric restriction of their diet, but only about dietary recommendations to follow the specific diet. In addition to the volunteer’s energy requirements, diets will take into account their food preferences and culture.

A weekly meal general plan, including portion sizes and a list of food equivalents will be provided to participants in both groups, so they could adapt and personalize their menus. The dietary prescription will be also easily accessible by both adolescents and their parents through an educational web-application developed by UNIPR partner. In addition, parents will be provided with a daily recipe to facilitate the adherence to the dietary prescription as well as to increase their culinary skills and the engagement in the project. Moreover, in each country, some recipes will be traditional of another country, i.e., a Spanish recipe in Italy or an Italian plate in Portugal.

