### 2.5. Educational Web-Application

The adolescents of both groups and their parents will have access to an educational web-application to be used during the intervention, where they can learn about health, nutrition, and food in general, how the right food choices positively impact on health, in addition to providing information on sustainability issues and the link between health and sustainability. The application will be developed as a cross-browser web-application with responsive design, so it will be available for both desktop and mobile devices. The application will be accessible at a specified secure URL and will require a username and a password to enter in the main page. The URL and the personal username and password will be provided to each participant at the beginning of the intervention period. Internet will be needed to use the application, independently if they use a computer, a smartphone, or a tablet. To ensure the validation and usability of the web-application, a pilot study will be performed in Italy with teenagers aged 13–17 years. The web-application will be intended for two final user typologies, namely the adolescent participant user and the parent user. For each one of the two users, specific contents will be available on the basis of the intervention group to which they will be assigned (MD or control group). The application will be designed to be used independently in Spanish, Italian, and Portuguese.

For the adolescents allocated to the MD group, the application will also include specific contents about MD, including information about pomegranate juice, hummus/chickpeas, mixed nuts, and sourdough bread.

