Some potential limitations need to be taken into account. First, while volunteers in the MD group will receive some foods to be included in their diet, volunteers in the control group will not, so adherence to the low-fat control diet may be lower. Second, due to the nature of the interventions, participants and dietitians/nutritionists cannot be blinded, although researchers who will perform all biochemical and -omics determinations as well as statistical analyses will be. Another limitation is the short follow-up period (4 months) that might limit conclusions on the long-term effects. On the other hand, the major strengths of the study can be listed: (a) this is the first large RCT to evaluate the health benefits of the MD against youth obesity and associated CVD risk factors, with a total of 240 volunteers; (b) this is a multicentric study carried out in three different Mediterranean countries, which facilitates the generalization of the conclusions achieved from this study; (c) adherence in both groups will be fostered through the availability of an educational web-application intended to be used by both parents and adolescents, which provides information related to health and nutrition as well as recipes, and that will allow a “learning-through-playing” approach; (d) the use of food intake biomarkers provides an objective assessment of adherence to dietary interventions and a robust measurement of the dietary pattern of the volunteers; and (e) the application of omics technologies and a systems biology approach, together with the wide range of biomarkers analyzed, will provide a significant progress in the current knowledge on the mechanisms implicated in the beneficial effects of MD as well as the role of gut microbiota in these effects.

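### The baseline visit (V1) is scheduled after randomisation in an open-label trial, and nothing stated protects the baseline values from knowledge of the arm

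*Protocol article*

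**What the plan says.** Everything here is in the protocol article.

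- **Visit order (Table 3).** V0 is the "pre-screening visit before randomization", and its only stated purpose is "To check inclusion/exclusion criteria in the study". V1 is "after randomization, inclusion visit", and it is the first visit with samples, anthropometry, blood pressure, questionnaires and dietary records.
- **Variables (Table 2).** Every listed variable with a timeline starts at V1. Dietitians/nutritionists take the anthropometry and blood pressure. A footnote says that the questionnaires and the 3-day record are collected through the app.
- **Blinding.** Section 2.1 says that "the participants cannot be blinded to the intervention". The Discussion says that "participants and dietitians/nutritionists cannot be blinded"; the blinded staff are those doing the laboratory determinations and the statistical analysis.
- **App (section 2.5).** For adolescents and parents, "specific contents will be available on the basis of the intervention group to which they will be assigned". Login details are issued when the intervention period starts.
- **Analysis (section 2.9.1).** The end-point ANCOVA for anthropometric and biochemical parameters models the change from baseline, adjusted for age, sex and the baseline value. Analyses are by intention-to-treat.
- **Eligibility (section 2.2).** To decide inclusion, "a medical interview, a physical examination, and laboratory tests will be performed", and inclusion depends on BMI percentile.

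**The concern.** A baseline covariate is safe to adjust for because allocation cannot have influenced it. Measuring it after randomisation, in people who may already know their arm, removes that guarantee.

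Four routes are open between randomisation and the end of V1:

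1. Adolescents who know their diet may answer diet, activity or quality-of-life questions differently.
2. They may already have started to change what they eat, which would also reach feces, urine and blood.
3. Unblinded dietitians take the physical measurements.
4. Some of those randomised may not come to V1, and not equally in the two arms. The Discussion itself notes that only the MD arm receives foods.

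On the first three routes, a baseline difference caused by allocation is treated as a chance imbalance and adjusted away, which distorts the estimated effect. On the fourth, a person has no V1 value from which to compute a change, which sits badly with an intention-to-treat analysis. Most of the affected baselines (microbiota, metabolites, diet records, questionnaires) have no scheduled measurement before randomisation, so later analysis could not recover them.

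**Working it through.** **Is V1 the baseline?** Table 3 gives V0 an eligibility purpose only, Table 2 begins at V1, and nothing names a V0 value as baseline. V1 is therefore the baseline by default.

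**Is V1 shielded from the arm?** Participants and dietitians are unblinded, and the app used for the V1 questionnaires carries content by arm and opens at the start of the intervention. No sentence places the V1 assessments before disclosure. Knowledge of the arm at V1 is plausible but not stated.

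**The plan's own figure.** The planned difference in BMI z-score is 0.2, with SD 0.5, two-sided alpha 0.05, 80% power and 20% dropout (section 2.8).

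- Per arm: 2 × [0.5 × (1.960 + 0.842) / 0.2]² = 98.1, or 196.2 in total.
- Dropout: 196.2 / 0.8 = 245.3. Rounding up to 99 per arm and multiplying gives 198 × 1.2 = 237.6.
- With 240 recruited and 20% lost, 96 per arm remain and power is 79.1%.

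The stated 240 is reproduced closely enough and is not in dispute. The 0.2 serves below as the yardstick.

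**Bias formula.** Let b be the slope of the final value on the baseline value, D_Y the arm difference (MD minus control) in final value, and D_X the arm difference in baseline.

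- ANCOVA on the final value estimates D_Y - b × D_X.
- ANCOVA on the change estimates (D_Y - D_X) - (b - 1) × D_X = D_Y - b × D_X, which is the same.

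If allocation adds a shift d to D_X, the estimate moves by -b × d. An unadjusted change score would move by -d.

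**Size for BMI z-score.** The article gives neither d nor b. Assume d of 0.02 to 0.05 and b of 0.7 to 1.0.

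| d | b = 0.7 | b = 1.0 | share of 0.2 |
|---|---|---|---|
| 0.02 | 0.014 | 0.020 | 7% to 10% |
| 0.05 | 0.035 | 0.050 | 18% to 25% |

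Direction depends on the sign of d. If the MD arm is lower at V1 because of early change, its benefit is understated. If it is higher, the benefit is overstated by the same amount.

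**Effect on the test.** Take b = 1, SD 0.5 and 96 per arm. The standard error is 0.5 × √(2/96) = 0.072. The two-sided type I error then rises from 5% to about 5.9% for d = 0.02 and 10.7% for d = 0.05.

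**Loss before V1.** If a fraction p of one arm is lost and those lost differ from those who stay by g in mean outcome, the arm mean is off by p × g. With p of 5% to 15% and g of 0.25 to 0.5 (both assumed), this runs from 0.05 × 0.25 = 0.0125 to 0.15 × 0.5 = 0.075, or 6% to 38% of 0.2.

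**The case against.** **Disclosure at V1 is not shown.** The blinding statements say that the intervention cannot be masked, not when each person learns the allocation. The unit that randomises is separate from the researchers. Measuring first and disclosing later in the same visit would fit the text, Figure 1 is not available, and a full protocol may settle the order. This stands: the defect is missing protection, not demonstrated bias. It does not remove the point, because the article does state the visit order, and an analysis plan cannot reorder visits.

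**The primary outcome is robust.** BMI z-score comes from measured weight and height, and a short wait should move it little. This largely stands. The interval from randomisation to V1 is not given, so a small d is the reasonable assumption. Nothing in the article supports a shift as large as half the planned effect.

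**A BMI exists before randomisation.** Eligibility depends on BMI percentile, so V0 must yield one. This stands and provides a fallback. The plan does not use that BMI as baseline, and the other outcomes have no such value scheduled.

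Some stronger readings are tempting but unsupported:

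- *All covariates may depend on the arm.* Age and sex cannot; only the baseline value can.
- *Baseline is both covariate and subtrahend, so the harm is doubled.* The algebra above shows that it is not.
- *The ANCOVA bias can be put in KidMed points.* Section 2.9.1 states that model for anthropometric and biochemical parameters only.
- *Energy targets become confounded with diet.* Section 2.3 says that "the level of physical activity will be obtained from the validated Physical Activity Questionnaire for Adolescents (PAQ-A" but does not say at which visit. Individual judgement by unblinded dietitians would also remain whatever the timing of V1. That is a separate question.

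**Conclusion.** The concern holds in a limited form. The article places the baseline after randomisation, in unblinded participants with unblinded measurers, and states no safeguard. Self-reported outcomes (KidMed, PAQ-A, food frequency, 3-day records, Kidscreen-27) are most at risk. Samples could be affected through early diet change, and measured BMI z-score is less exposed.

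For the primary outcome the bias is 0.014 to 0.05 in size, or 7% to 25% of the planned difference, if d is 0.02 to 0.05 and b is 0.7 to 1.0. Both ranges are assumptions, and either direction is possible. A reader might infer that the baseline is already compromised or that the primary result would be invalid; the article supports neither, because it is silent on when the allocation is disclosed. This should be fixed, since the remedy is cheap and most of the baselines could not be recovered afterwards. It is not a fatal flaw.

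**What to change.** 1. Complete all V1 measurements, samples, questionnaires and the 3-day record before randomisation, or at least before the allocation is disclosed to participant, family and dietitian.
2. Give neutral app access for the baseline questionnaires and record, and open the arm-specific content only after disclosure.
3. Correct the V1 label in Table 3 to match. If practice already follows this order, correcting the label and adding a sentence on when the allocation is disclosed settles the matter.
4. If V1 must stay after randomisation, name the V0 BMI as the baseline for the primary outcome. Keep everyone randomised in the intention-to-treat set whether or not they attend V1. This protects the primary outcome only.

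**Cost.** The sample size stays at 240 and no visit is added. A 3-day record cannot be finished within one visit, so neutral app access is needed some days earlier. Menus and food supply would be prepared after V1. The fallback also requires weight and height at V0 to be measured to the same standard as at later visits.

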## Data Availability

No new data were created or analyzed in this study. Data sharing is not applicable to this article.
